### Limitations

One major limitation of this study is the sample size and distribution. Although many patients participate in our institutional MAC registry, the inclusion criteria narrow down the eligible patients. Furthermore, the willingness of participants was lower than expected, which influenced the distribution of age and sex within the different groups. Whether these variations in baseline characteristics do influence the identification of acoustic biomarkers with a prognostic value for early-stage osteoarthritis, remains unclear until the data analysis has been completed. Still, the sample size is significantly larger than most comparable studies [20] and in line with the most relevant references in the state-of-the-art [16].

A second limitation of the study is the recruitment of patients postsurgery reconstruction. We decided to choose this patient population, as they have a higher predisposition to develop osteoarthritis; however, it might limit the generalization of the approach to highly active individuals who are more prone to injury. Furthermore, while having a balanced age and BMI between groups reduces the impact of covariates, it also limits the generalization of the approach to populations with different osteoarthritis phenotypes. To further enhance the approach’s potential, this pilot study should be applied to other centers for data collection to expand the sample size for validation with other osteoarthritis populations with different backgrounds.

Another concern is that resulting acoustic biomarkers may mostly reflect movement patterns rather than a causal relation to osteoarthritis. This critical aspect has been carefully considered in the design of the experimental protocol. As described in the study procedures section, the exercises (movements) the participants must perform are extremely standardized. Also, we will have the kinematic data associated with any potentially discriminative AEs. This allows us to study any movement patterns that may be associated with acoustic biomarkers and assess how strongly they are correlated with specific movements that may not be specific for osteoarthritis. Also, on top of the IMU in the device, sit-to-stand is performed on force plates, so an imbalanced load could also be accounted for in the models. On the other hand, we believe that finding movement patterns that are strongly correlated with the osteoarthritis gradings would be a very relevant contribution of the study, even if causal links cannot be directly established.

Finally, another limitation is the lack of medical history. Although patients are screened and asked about revision or previous surgeries as well as former injuries of the comparator knee, there is no guarantee a patient has not already been operated on or operated on again at a different hospital.

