Unloaded flexion-extension (F-E) of the knee in a seated position, starting with a knee angle of 90°, followed by a full extension and returning to the starting position (6 times). A video will guide the pace of the motion to normalize the velocity among patients (comfortable speed).Sit-to-stand test (STS) at a comfortable pace (6 times). Force plates (FP-BTA; Vernier) will be used during this exercise to assess the ground reaction force for each sole and detect any asymmetrical loading of the joints.One-step test (OST) is an exercise step platform, which will be used to perform a complete ascent and descent at a comfortable speed (6 times per leg).Walk test at a comfortable pace (10m ×2 times).

The following measurements will be performed together with the AE tests:

Temperature assessment: thermal distribution of the knee joint will be assessed with a far infrared thermal sensor array (MLX90640; Melexis) to evaluate the state of inflammation. Localized thermal images will be recorded at three time points: (1) at the beginning of the whole test, just after arriving, (2) after warming up (5 minutes on a stationary bicycle), and (3) at the end of all tests.Pain assessment: after the test session, the level of knee pain will be assessed using a visual analog scale. Participants will quantify the maximum knee pain experienced during the tests for each knee separately by placing a vertical mark on a 10 cm horizontal line. The line ranges from 0 (“no pain at all”) to 10 (“not endurable pain”).

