## Results

Recruitment and data collection started in December 2022. In November 2023, data collection has been completed for the first visit. The data collection for the second visit will end in 2024. Data processing and analysis are ongoing at the time of this writing.

Baseline data of study participants are shown in Table 3. The median age for the healthy controls (A) is slightly lower, and for the TKA group (D) slightly higher compared to the 2- and 5-year postoperative patients (B and C). Older patients in the TKA group (D) are reasonable, as TKA surgery is often the last option left for treatment. We do observe higher values for BMI in the poor postoperative outcome groups (B2 and C2) and the TKA group (D). Balanced sex distribution was not achieved in 2- and 5-year postoperative groups due to the low willingness to participate as well as the low numbers of female patients within our registry meeting all the inclusion criteria.

**Table 3. T3:** Baseline data of study participants.

Characteristic	A (n=20)	B1 (n=20)	B2 (n=20)	C1 (n=20)	C2 (n=20)	D (n=20)
Age, mean (SD)	46 (7)	50 (8)	54 (8)	52 (7)	52 (7)	67 (7)
BMI, mean (SD)	24.25 (2.82)	24.75 (2.75)	26.05 (2.44)	24.65 (2.31)	26.00 (3.71)	26.35 (3.99)
Sex, n (%)						
Female	10 (50)	9 (45)	8 (40)	6 (30)	6 (30)	10 (50)
Male	10 (50)	11 (55)	12 (60)	14 (70)	14 (70)	10 (50)

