## Discussion

### Principal Findings

This exploratory study aims to identify biomarkers with a prognostic value in the prediction of osteoarthritis. Acoustic, kinematic, and thermal features will be extracted and combined with an artificial intelligence algorithm, and evaluated against gold-standard osteoarthritis diagnosis, such as radiographs and MRI. Some candidate acoustic biomarkers have been identified in a preliminary study [9], using a multifractal analysis method. However, multiple other candidates will be evaluated individually or in combination in our study. Therefore, the primary endpoint can be defined as the area under the curve of the receiver operating characteristic analysis of each biomarker or combination of biomarkers in the regression analysis, finally identifying the parameters with the highest sensitivity and specificity to predict early-stage osteoarthritis in clinical use. AE is patient-dependent, and as such, demographic and baseline health data will be captured and entered as covariates in the regression models. The secondary objective is to evaluate the value of these biomarkers in predicting osteoarthritis evolution. For this objective, the patients will be examined a second time at 9-month intervals, and the new biomarkers will be introduced in regression models to evaluate the predicted performance for osteoarthritis evolution.

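### Age is called balanced between groups, yet Table 3 shows mean ages from 46 to 67; with age entered as a covariate, a combined model's AUC can rise without acoustic information

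*Protocol article*

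**What the plan says.** **Balance.** Discussion, Limitations: "while having a balanced age and BMI between groups reduces the impact of covariates". Results, on age: "for the TKA group (D) slightly higher compared to the 2- and 5-year postoperative patients". That sentence speaks of medians, but Table 3 beneath it gives means and SDs. On BMI the Results say: "We do observe higher values for BMI in the poor postoperative outcome groups (B2 and C2) and the TKA group (D". Limitations also concedes that low willingness to take part affected the age and sex distribution.

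**Eligibility.** Textbox 1 admits Groups A, B and C at 35 to 65 years and Group D at 35 to 75.

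**Endpoint and covariates.** Principal Findings defines the primary endpoint as the ROC area of each biomarker, or combination of biomarkers, in the regression analysis, and adds that "demographic and baseline health data will be captured and entered as covariates in the regression models". Kinematic and thermal features are to be combined with the acoustic ones. Feature Analysis and Multivariate Modeling makes the KL or MOAKS grade the dependent variable, plans to assess the relevance of confounders such as age and BMI, and relies on leave-one-subject-out nested cross-validation.

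**Movement.** Limitations says "the exercises (movements) the participants must perform are extremely standardized". In the description of the functional tests, only flexion-extension is paced by a video. The others are self-paced, for example "Sit-to-stand test (STS) at a comfortable pace (6 times"; the step and walk tests are likewise at a comfortable speed.

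**The concern.** The balance sentence is the article's reason for expecting covariates to matter little. If age is far from balanced, that reason falls away, and the definition of the primary endpoint matters more.

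Entering age in a logistic model adjusts the coefficient of an acoustic feature. It does not take age out of the model's AUC, because the fitted score uses age to rank knees. A combined model can therefore discriminate well while its acoustic terms contribute nothing. Cross-validation does not protect against this: it guards against overfitting, whereas the age difference is a real feature of the sample that recurs in every fold.

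At stake is the attribution of the result. The stated aim is acoustic biomarkers for early detection, so the useful quantity is what sound adds to information a clinician already has.

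**Working it through.** **Inputs (Table 3, n = 20 per group).** Age, mean (SD): A 46 (7), B1 50 (8), B2 54 (8), C1 52 (7), C2 52 (7), D 67 (7). The article gives no balance test or age-only AUC to reproduce, so the check starts from these figures.

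**1. Age across six groups.** Grand mean = 321/6 = 53.5.
- Between-group SS = 20 × (56.25 + 12.25 + 0.25 + 2.25 + 2.25 + 182.25) = 20 × 255.5 = 5110, so MS = 5110/5 = 1022.
- Within-group SS = 19 × (49 + 64 + 64 + 49 + 49 + 49) = 6156, so MS = 6156/114 = 54.
- F(5,114) = 1022/54 = 18.9, P about 1e-13. Eta-squared = 5110/11266 = 0.45.

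D minus A is 21 years, or 3 SD. D minus B2, the next oldest group, is 13 years (Welch t = 13/√(49/20 + 64/20) = 5.47, P about 3e-6).

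**2. Without Group D.** A to C span 54 − 46 = 8 years. Between-group MS = 736/4 = 184 and within-group MS = 55, so F(4,95) = 3.35, P = .013, eta-squared 0.12.

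**3. BMI, six groups.** From the Table 3 means and SDs in the same way: F = 1.69, P = .14, eta-squared 0.07. The fault in the balance sentence is therefore mainly about age.

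**4. Age overlap.** With D taken as normal (67, 7), P(age > 65) = Φ(2/7) = 0.61. Truncating at the eligibility limit of 75 gives (0.8735 − 0.3875)/0.8735 = 0.56. About 56–61% of D would be older than the eligibility limit of every other group.

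**5. Age-only AUC for group labels.** Assuming normal ages, AUC = Φ((μ₁ − μ₂)/√(s₁² + s₂²)), averaged over group pairs.
- D vs A: Φ(21/√98) = 0.98.
- D vs each of A, B1, B2, C1, C2: 0.983, 0.945, 0.889, 0.935, 0.935; average 0.94.
- B + C vs A: 0.72. B2 + C2 vs A + B1 + C1: 0.63. B2 + C2 vs B1 + C1: 0.57.

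**6. Age-only AUC per knee.** The endpoint concerns KL or MOAKS grade, and both knees are examined. The article does not give the grade distribution, so shares were assumed: every D index knee has osteoarthritis (OA), A knees and unoperated B/C knees have none, and the other two shares vary. Simulated means (600 replicates per cell):

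| OA in D contralateral knees | 0% of operated B/C knees | 20% | 50% |
|---|---|---|---|
| 0% | 0.90 | 0.72 | 0.63 |
| 50% | 0.92 | 0.78 | 0.69 |
| 100% | 0.94 | 0.83 | 0.75 |

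Across the same grid, a single feature with no OA signal but an assumed correlation of 0.5 with age reaches 0.57 to 0.73.

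**7. Effect of leave-one-subject-out validation.** Logistic regression, 20% OA in operated B/C knees, 60 replicates. With 0% OA in D contralateral knees, age alone gives 0.70 and age plus a pure-noise feature 0.69. With 50%, both give 0.77. Validation leaves the age contribution in place. Noise alone gave 0.33 and 0.38, below 0.5, so the covariates-only model in the same folds is a better reference here than 0.5.

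**8. Movement.** One of four tests is externally paced. The article gives no figures from which a speed effect could be sized.

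**The case against.** **The balance sentence may mean Groups B and C only.** It closes a paragraph about recruiting patients after reconstructive surgery. Among B1 to C2 the data would support it: age F(3,76) = 0.94, P = .42; BMI F = 1.44, P = .24. But the sentence speaks of groups without restriction, the same section concedes that the age distribution was affected, and the Results separately describe a 13- to 17-year difference between D and the B/C groups as slight.

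**Age differences are disclosed and covariates are planned.** This is true and counts in the article's favour: the directions are reported and confounders will be assessed. It does not change what a combined model's AUC contains once age is in it.

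**A covariates-only comparator is analysis-plan detail.** Its absence from an article would not be a finding in itself. The point is that the endpoint, as defined, credits age to the combined model, while the article plays covariates down on the strength of an incorrect statement.

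**Stronger readings that the article does not support:**
- A reader might take 0.98 or 0.94 as the age-only value of the primary endpoint. These classify group labels. A person's two knees share one age, so age cannot separate them, and the knee-level figure may be much lower.
- A reader might infer that the study cannot show whether sound adds information. Single-feature analyses are planned, age enters those only through age-related features, and the data for a proper comparison are collected.
- A reader might infer that Group D has no age overlap with the rest. Under the normal approximation, 39–44% of D is 65 or younger.
- A reader might infer that movement is uncontrolled. Flexion-extension is paced, Limitations already plans to relate acoustic features to kinematics, force plates record loading in sit-to-stand, and the confounder list is given as examples only.

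**Conclusion.** The concern holds in a limited form. The statements that age is balanced and that D is slightly older are contradicted by Table 3. The BMI part of the sentence is only weakly contradicted.

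For combined models, the primary AUC can be raised by age without acoustic information. The size is uncertain: about 0.63 to 0.94 per knee for age alone, depending on assumed OA shares, a binary split of the grade and normally distributed ages. The problem is largest when Group D is included. The article does not show that its eventual AUC will in fact be driven by age.

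The movement point is secondary. The claim of extreme standardization fits one test of four, and what is needed extends a check the article already intends.

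**What to change.** 1. Correct the balance sentence in Limitations and the wording on Group D's age in the Results. State the range of means, and refer to means, as Table 3 does.
2. For every multivariable model, report the cross-validated AUC of a covariates-only model (age, sex, BMI) in the same folds, and the gain from adding acoustic features, with a subject-level bootstrap interval. Treat the gain as the evidence about sound.
3. Repeat step 2 without Group D, where age overlap with the other groups is limited.
4. For sit-to-stand, step and walk tests, add IMU-derived movement speed to the comparator model, and restrict the claim of extreme standardization to the video-paced test.

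**Cost.** One further model per analysis, on data already in the visit schedule. The reported gain will be smaller than the raw AUC, and the analysis without D rests on 100 participants instead of 120, so it is less precise.

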### Conclusion

The reference database that will be gathered by this study in a subpopulation at risk of developing osteoarthritis will help to further explore the potential of acoustic biomarkers to diagnose osteoarthritis at earlier stages. A noninvasive knee sound diagnostic tool could provide a better understanding of the disease and its progression at low cost and without radiation exposure. Therefore, this study will contribute to improved clinical decision-making and enable preventive measures.
